### Comparator (intervention-light)

Nurses at intervention-light sites will be managed according to what would currently be regarded as best practice, with provision of an advice leaflet about optimal hand care entitled ‘Dermatitis: occupational aspects of management. Evidence-based guidance for employees’ (also provided to the intervention-plus group) and encouragement to contact their OH department early if hand dermatitis occurs. However, they will not receive the BCP or active reinforcement of its messages. Nor will they routinely be offered supplies of moisturising cream over and above what is already standard practice at their site.

### Sampling

We identified all NHS sites in the UK that train nurses, have an in-house OH service, and have at least one ICU. We first wrote to the lead occupational physician in each eligible site in December 2011, asking their willingness, in principle, to collaborate in a trial; and we wrote again in May 2012 and January 2014 asking them to confirm their willingness to collaborate. We also invited additional sites to sign up to the study via national OH newsletters. This included some sites that had an ICU but did not train nurses, and vice versa. In order to avoid the risk of student nurses moving placements from an intervention to a control site (or vice versa) during the study period, we generally invited only one site in each city or town to participate in the study. The exceptions were London and Manchester. In London, three sites were identified in which student nurses did not move to neighbouring sites during their training. In Manchester, we identified sites where students at three local universities undertake their clinical placements during their first year of nursing training, and ensured that these sites were clustered appropriately to prevent cross-contamination in the study.

A summary of the number of participating sites is provided below:12 sites recruiting both ICU nurses and student nurses (NHS trusts/health boards)18 sites recruiting ICU nurses only (NHS trusts/health boards)5 sites recruiting student nurses only (university-based OH departments)

#### Study group 1 – student nurses

All student nurses are required to attend for OH assessment before starting their clinical work. At participating sites, with permission from the universities concerned, all student nurses in one or more year groups (excluding mental health nursing students) who are due to start their first clinical placement, will be sent a Participant Information Sheet by their university or their OH department before or at the time of their mandatory assessment. Those who have a history of atopic disease or hand eczema will be identified by the OH department at the assessment, from information that they provide in a generic pre-placement health screening questionnaire. An OH clinician will explain to them that because of their constitution, they are at increased risk of hand dermatitis and, therefore, need to take special care of their hands. Those student nurses who meet the inclusion criteria will then be invited to participate in the study. A field worker will obtain written consent from those nurses who agree (the lead OH practitioner at the study site and the trial manager being available if needed to answer any questions). The consent form will ask participants to provide a preferred email address and telephone number to facilitate follow-up, and so that those at intervention-plus sites can be sent a link to the online BCP. One copy of the signed consent form will be filed in the nurse’s OH notes, one copy will be sent to the trial manager, and a third copy will be given to the participant. Participants will also be provided with an information sheet to give to their general practitioner.

#### Study group 2 – intensive care nurses

The investigators, trial manager and lead OH clinicians from each site will identify all ICUs (and a few also identified their special care baby units) that would be suitable for the study. A local OH clinician or senior ICU nurse will explain to all nurses working on the selected ICUs that they are at increased risk of hand dermatitis because of frequent hand-washing with cleansers and water. They will also be told that a study is being carried out to help optimise management of nurses who are higher risk. Full-time ICU nurses in the ICU (those working at least 30 hours per week) will be provided with a Participant Information Sheet and will be given up to a week to decide whether they wish to participate in the study. Consent to take part will be obtained by the field worker, who along with the trial manager, will be available to answer any queries about the study. The consent form will ask participants to provide a preferred email address to facilitate follow-up, and so that those at intervention-plus sites can be sent a link to the online BCP. Participants will be provided with an information sheet to give to their general practitioner.

The study will be presented to both study groups as research to assess the causes, consequences and ways of preventing hand dermatitis in nurses who are at increased risk, either because of a personal history of atopy or eczema, or because of the type of work that they do. However, to minimise the chance of bias, they will not be told that they are in an intervention-plus or intervention-light group. During the recruitment phase, field workers will reinforce the importance that participants be able to commit fully to the study, particularly with respect to the completion of questionnaires (see below).

To check that rates of participation do not differ importantly between sites randomised to the two arms of the study, the recruitment process will be carefully documented. The total numbers of eligible student and ICU nurses will be recorded, as will the numbers who consent to take part. We will also record the numbers who drop out of the study, with the dates of drop out.

### Data handling

Data from the trial will be handled by InferMed MACRO v4 and data entry and handling will be audited.

### Randomisation

Randomisation will be carried out using fixed blocks of two, stratified by small or large site with or without student nurses. Two sites will be randomised at a time and the King’s Clinical Trials Unit will control the order of the randomisation in order to ensure allocation concealment. Baseline will be collected prior to randomisation.

For the purpose of analyses by intention-to-treat, the date of entry into the study for each participant will be date when they sign the consent form. Although student nurses can only contribute useful information if they progress to clinical work, in practice very few fail to do so once they have begun their nursing studies.

Members of the study team will be notified of the outcome of randomisation in a blinded or unblinded manner, according to their role in the trial. The trial statistician (GN), methodologist (DC), and the dermatologists (HW, JE) will remain blinded to treatment allocation until after the primary analysis.

### Sample size

Field workers will be encouraged to recruit as many eligible student nurses and ICU nurses as possible, with the aim of recruiting at least 40 student nurses and 40 nurses from the ICUs at each site.

To give an indication of power, we assumed that at the end of follow-up the expected prevalence rates overall at the intervention-light sites would be 24 % in both student and ICU nurses, that the intraclass correlation coefficient (ICC) is 0.05 (this corresponds to a variance inflation factor of 2.05 for student nurses and 2.8 for ICU nurses), and that 20 % of participants will be lost to follow-up. With a 5 % level of statistical significance (two-sided), we would have approximately 83 % power to detect a reduction in prevalence of dermatitis at follow-up in the intervention-plus sites to 10 % in student nurses and 91 % power to detect a reduction in prevalence to 10 % at follow-up in ICU nurses. For final prevalence rates of 12 %, the powers would be 68 % for student nurses and 78 % for ICU nurses, while for final prevalence rates of 14 %, the corresponding powers would be 51 % and 61 % respectively. The power will be higher if the ICC is lower than 0.05. (These calculations were carried out using the clustersampsi command in Stata v12.1 for difference in proportions.)

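### The stated 83 % power for student nurses is not reached with the 17 student sites listed, and the stated variance inflation factors do not match the recruitment target of 40 per site

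*Protocol article*

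**What the plan says.** All references are to the protocol article. Under Sample size, field workers recruit as many as they can, "with the aim of recruiting at least 40 student nurses and 40 nurses from the ICUs at each site". The power statement assumes that "the expected prevalence rates overall at the intervention-light sites would be 24 % in both student and ICU nurses", an ICC of 0.05 and 20 % loss to follow-up. It adds that "this corresponds to a variance inflation factor of 2.05 for student nurses and 2.8 for ICU nurses". At the two-sided 5 % level it claims "approximately 83 % power to detect a reduction in prevalence of dermatitis at follow-up in the intervention-plus sites to 10 % in student nurses". The matching claim for the ICU group is 91 %. For a smaller effect the section continues: "For final prevalence rates of 12 %, the powers would be 68 % for student nurses and 78 % for ICU nurses". At a final prevalence of 14 % its figures are 51 % (students) and 61 % (ICU). The calculation is attributed to a Stata command for clustered differences in proportions. The number of sites entered is not given.

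The concise statement of the research and the Sampling section both list 12 sites recruiting both groups, 18 recruiting ICU nurses only and 5 recruiting students only. That makes 12 + 5 = 17 student sites and 12 + 18 = 30 ICU sites. Under Data analysis, outcomes are to be assessed separately in the two groups.

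**The concern.** Two statements do not fit together. First, the variance inflation factors (VIFs) differ between the groups and imply clusters of 22 and 37, although the recruitment aim is the same 40 for both. Second, students have little more than half as many sites as ICU nurses and, on the implied sizes, smaller clusters, yet the claimed student power is only 8 points lower (83 % against 91 %).

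The groups are analysed separately and each has its own principal outcome, so the student comparison has to carry its own power. If 83 % is wrong, readers will judge a student result, and a null one in particular, against a sensitivity that the design does not have.

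**Working it through.** **Inputs.** From Sample size: two-sided alpha 0.05; control prevalence 24 %; intervention prevalence 10, 12 or 14 %; ICC 0.05; loss 20 %; VIFs 2.05 and 2.8; aim of 40 per site. From Sampling: 17 student and 30 ICU sites. From Randomisation: blocks of two, so about 8.5 student sites and 15 ICU sites per arm. A 9 v 8 split moves the results by about one point.

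**Cluster sizes implied by the VIFs.** VIF = 1 + (m − 1) × 0.05, so m = 1 + (VIF − 1)/0.05.
- Students: 1 + 1.05/0.05 = 22.
- ICU: 1 + 1.80/0.05 = 37.
- At 40 recruited: VIF = 1 + 39 × 0.05 = 2.95. At 40 × 0.8 = 32 analysed: 1 + 31 × 0.05 = 2.55. Both apply equally to the two groups, and neither stated VIF equals either value.

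**Power formula.** Effective n per arm = sites per arm × analysed per site / VIF. Power follows from z = difference/SE − critical value, with SE² = (p₁(1 − p₁) + p₂(1 − p₂))/n. The ranges below cover normal approximations (pooled and unpooled variance) and t approximations (central and non-central) with sites − 2 degrees of freedom.

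**Reproducing the ICU figures first.** 30 sites, 37 recruited, 29.6 analysed, VIF 2.8: n = 15 × 29.6/2.8 = 158.6. Pooled normal gives 91.7/79.7/62.3 % and non-central t gives 90.3/77.6/59.9 %. Stated: 91/78/61 %. The method reproduces them.

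**Students at 17 sites** (stated: 83/68/51 %):

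| Scenario | Effective n per arm | Normal, 10/12/14 % | t (15 df), 10/12/14 % |
|---|---|---|---|
| 22 recruited, 17.6 analysed, VIF 2.05 | 8.5 × 17.6/2.05 = 73.0 | 62–63 / 47–48 / 34 | 56–57 / 41–43 / 29–31 |
| 22 analysed, VIF 2.05 | 8.5 × 22/2.05 = 91.2 | 71–73 / 56–57 / 40–41 | 66–67 / 50–52 / 35–37 |
| 40 recruited, 32 analysed, VIF 2.55 | 8.5 × 32/2.55 = 106.7 | 78–79 / 63–64 / 46–47 | 73–74 / 57–58 / 40–42 |

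Worked line for the last row at 10 %: SE = √((0.24 × 0.76 + 0.10 × 0.90)/106.7) = 0.0505, and 0.14/0.0505 = 2.77. Then 2.77 − 1.96 = 0.81, which gives 79 %. With t on 15 df, 2.77 − 2.13 = 0.64, which gives 73 %.

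If the first row's VIF is reset to its analysed size (1 + 16.6 × 0.05 = 1.83), power at 10 % is about 61–68 %, still inside the overall range.

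**Sites needed for 83 % at 10 %.** About 19–21 with 32 analysed; about 22–25 with 22 analysed; about 28–30 with 22 recruited and 20 % lost.

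**The case against.** The strongest reply is that the figures are offered only as an indication of power, that 40 is an aim rather than a planning value, and that the VIFs are never said to derive from it. Planning on clusters smaller than the aim is legitimate. This stands as far as it goes: the VIFs need not be wrong if the intended sizes were 22 and 37. But the document should then say so, and with clusters of 22 the student shortfall is larger, not smaller.

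A second reply is that some pairings come close at 17 sites. With 32 analysed and VIF 2.05, a non-central t gives 82.3/67.3/50 %. With 40 analysed and VIF 2.95, the normal approximation gives 81–82 % at 10 %. Each breaks a stated input. VIF 2.05 does not belong to 32 per site at ICC 0.05, and correcting it to 2.55 returns 73–79 %. The other pairing ignores the 20 % loss. These near-fits do show that the site count behind the calculation cannot be recovered uniquely. At 30 sites, with 22 recruited and 20 % lost, the student figures come out at 83.6/68.8/51.3 %, so a reader might infer that the ICU site count was applied to students. That is possible but not shown, and the point does not need it.

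Third, the planned model adjusts for baseline dermatitis, which could add power, as could recruiting above 40. The power paragraph credits neither. In the other direction, unequal site sizes would lower power, and the Discussion reports lower recruitment than expected at some sites.

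**Conclusion.** The stated student powers of 83/68/51 % are not supported by the document's own inputs. For a fall to 10 %, 17 sites give about 56–63 % (22 recruited), 66–73 % (22 analysed) or 73–79 % (40 recruited, 32 analysed). The last case, which is the stated recruitment aim, gives 57–64 % at 12 % and 40–47 % at 14 %. This rests on ICC 0.05, 20 % loss, near-equal allocation of sites, equal cluster sizes and no gain from covariate adjustment.

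Three stronger readings should be resisted:
- That 22 to 30 student sites are required. This holds only for clusters of 22; at the recruitment aim the gap is about 2 to 4 sites.
- That the ICU power is also wrong. It is supported at 30 sites.
- That a null student result could not exclude a reduction to 12–14 %. What a result excludes depends on the observed confidence interval, not on design power.

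**What to change.** In the Sample size section, give for each group the number of sites (17 student, 30 ICU), the analysed cluster size after 20 % loss, and the VIF that follows from that size at ICC 0.05. State whether the planning size is the aim of 40 or something smaller. Replace 83/68/51 % by the recomputed student powers, for example about 73–79/57–64/40–47 % if 32 are analysed per site. An allowance for unequal site sizes and a t reference are optional refinements.

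The cost is one rewritten paragraph and a less favourable student power. No extra recruitment or change of analysis follows from it.

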### Setting

OH departments (NHS and university-based) in the United Kingdom (excluding a pilot site in Wales).

### Data collection

#### Study group 1 – student nurses

Student nurses who agree to take part will be asked to complete a self-administered baseline questionnaire (Questionnaire A) covering: contact details (which for security reasons will be kept separate from the rest of the questionnaire); demographic information; history of atopic disease and allergies; activities outside work which predispose to hand dermatitis; beliefs and plans regarding dermatitis prevention behaviours; the EuroQol-5D (EQ-5D) health-related quality of life questionnaire [36] and history of hand dermatitis ever, in the past 12 months, and currently. They will be asked to place the completed questionnaire into a sealed business reply envelope and return it to the SCIN research team in London via the field worker, or if they prefer, directly. In addition, they will be invited to have their hands and wrists photographed.

Participants will be told that they may be asked to access an online BCP, which they should undertake in the week before starting their first clinical attachment, and to which they will be sent a link (by email) 2 weeks before the attachment begins. At that time, they will also be sent (by post) a personal tube of moisturising cream with guidance on how to request further supplies if needed. All participants, at both intervention-plus and intervention-light sites, will be encouraged (orally, through a written advice leaflet, and by email reminders at 4 and 8 months) to attend their OH department at an early stage should they develop hand dermatitis.

One week after starting their first clinical attachment, all participants will be asked to complete a further short self-administered questionnaire (Questionnaire B), covering beliefs and plans regarding dermatitis prevention behaviours. At intervention-plus sites, it will also ask about use of, and views on, the BCP. Questionnaire B will be sent by post to participants with a business reply envelope for return to the SCIN research team.

To account for possible seasonal variation in the prevalence of dermatitis, final data collection will be carried out 12 months after baseline. All participants will be asked to answer a third self-administered questionnaire (Questionnaire C) and again to have their hands photographed. Questionnaire C will be distributed by the local field workers, and will cover: clinical attachments undertaken in the past year; hours worked per week over the past year; beliefs and plans regarding dermatitis prevention behaviours; participation in, and views about, the BCP (only at intervention-plus sites); activities outside work which predispose to hand dermatitis; recent practices regarding use of gloves; recent practices regarding hand cleansing; recent use of moisturising creams; history of hand dermatitis in the past 12 months (including its investigation and treatment, and any consequent loss of time from work or restriction of duties); and the EQ-5D questionnaire. Student nurses will be asked to place the completed Questionnaire C into a sealed business reply envelope for return to the SCIN team via the field worker or directly.

In addition, any attendance at OH with symptoms of hand/wrist dermatitis and any requests for extra provision of emollients during the study period will be documented.

#### Study group 2 – intensive care nurses

ICU nurses who agree to participate will be asked to complete a self-administered baseline questionnaire (Questionnaire A) similar to that for student nurses, but also including items on current occupation; recent practices regarding use of gloves; recent practices regarding hand cleansing; recent use of moisturising creams; and any sickness absence or modification of duties during the past 12 months because of hand dermatitis. Arrangements for the return of completed questionnaires will be as for student nurses. They will also have their hands and wrists photographed.

Once recruitment has been completed, field workers at intervention-plus sites will promote the importance of optimising equipment for hand cleansing, and dispensation of moisturising cream. The written leaflet about prevention of hand dermatitis will be made available to all staff on the ward (not only those individuals who have consented to take part in the study), and an email will be sent via the lead ICU nurses to all staff on the ward with a link to the BCP. Uptake of the BCP will be documented.

Following recruitment, all ICU nurses (not just those who have agreed to participate in the study) at intervention-light sites will also be given the written leaflet about prevention of hand dermatitis.

Two weeks after the BCP has been offered (or at a similar interval after recruitment in the intervention-light sites), participants will be asked to complete a second questionnaire (Questionnaire B) about beliefs regarding prevention of dermatitis and (at intervention-plus sites) participation in, and views on the BCP. Questionnaire B will be sent to participants by post with a business reply envelope. All participants at both the intervention-plus and intervention-light sites will be encouraged (orally, through the written advice leaflet and by email reminders sent out by the SCIN research team at 4 and 8 months) to attend the OH department at an early stage should they develop hand dermatitis. Email reminders will also contain a positive reinforcement message to encourage ongoing participation in the study. In addition, at the intervention sites, the email reminders will reinforce the BCP.

Outcomes will be assessed 12 months after baseline. All participants will be asked to complete a final self-administered questionnaire (Questionnaire C), and again to have their hands and wrists photographed. Questionnaire C will be sent out to field workers by the SCIN research team 2 months before the end of the study, and they in turn will pass them on to participants at the time that they recall them to have their hands photographed. The nurses will be asked to place the completed questionnaire into a sealed business reply envelope and return it via field worker or directly to the SCIN team in London.

### Withdrawal from the study

Participants who decide to withdraw from the study, for whatever reason, will be asked to complete a shortened version of Questionnaire C and will be invited to have follow-up photographs of their hands and wrists.

### Study instruments and data collection tools

#### Questionnaires

The study questionnaires have been developed specifically for this study, and piloted in a sample of 22 student nurses and 22 ICU nurses. Questions about dermatitis are derived from the Nordic Occupational Skin Questionnaire [37]. The EQ-5D health-related quality of life questionnaire [36] has been included and the questions on beliefs are based on the structure suggested for assessing TPB [38] and are informed by information we obtained from focus groups on student and ICU nurses.

Throughout the study, non-responders to any of the three study questionnaires will be sent an email reminder from the SCIN research team with a request that they complete and return the questionnaire directly to the SCIN team. If questionnaires remain outstanding, another copy of the paper questionnaire will be posted to the participant’s preferred postal address, along with a business reply envelope. If questionnaires remain outstanding after a further 2 weeks, participants will be sent up to two reminder text messages (or telephone messages if they have given a land line number).

At the end of the study period, participants who have completed and returned all three study questionnaires will be entered into a prize draw, giving them a chance to win one of the study cameras (a total of 26 cameras will be offered). Information about the draw and prizes will be included in the Participant Information Sheet.

